The primary objective of the trial is to evaluate the efficacy of the intervention in terms of left ventricular remodeling. This will be accomplished by quantifying the change in the Left Ventricular End-Diastolic Volume Index (LVESVI) at the time of hospitalization and at regular intervals following the procedural intervention, employing transthoracic echocardiography (TTE).

Secondary endpoints.

The main secondary endpoint is mortality, which will be evaluated based on the total number of deaths from any cause.

In addition to the primary endpoints, the trial has defined the following secondary endpoints:Perioperative management.

The variables to be evaluated are as follows: operative time, cardiopulmonary bypass time, cross-clamp time, blood loss, and transfusions.

○Cardiopulmonary bypass parameters.

Information pertaining to the elapsed time of myocardial ischemia, the duration of cardiopulmonary bypass, and the method of cardiac cardioplegia perfusion (retrograde or antegrade) will be extracted from the dataset.

○Blood loss and transfusions. Supplementary Table S1 [35,36,37]○Reoperation for bleeding. Supplementary Table S1 [35,36,37]

A reoperation to reopen the chest for the management of excessive bleeding is indicated in cases where bleeding persists. A reoperation for bleeding is defined as any subsequent surgical procedure necessitated by the necessity to address excessive bleeding in a patient in whom the sternum was left open during the initial operation. It is essential to recognize that reopening the chest for hemodynamic instability without severe bleeding and for the purpose of puncturing the pericardium or pleura or inserting a chest tube for retained blood syndrome is not regarded as a reoperation for bleeding.

▪Functional Status.•MACE (major adverse cardiac event).

A MACE is specified as an unweighted composite score. It consists of the following components:○Death.○Stroke.○Mitral valve re-intervention.○Worsening heart failure (+1 NYHA Class).○CHF hospitalization.•Reoperation.

All subsequent surgical procedures, including reoperations for MR, will be meticulously documented, and the incidence of reoperation will be evaluated through a rigorous time-to-event analysis.

Peak VO2.

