The inability to discontinue ventilatory support within 48 h after surgery, which necessitates re-intubation or tracheostomy, is indicative of respiratory function impairment. This definition does not pertain to instances where the patient is re-intubated for a further surgical procedure or where the patient is temporarily intubated for diagnostic or treatment purposes.

Bleeding.

An incident characterized by bleeding is any instance where one of the following occurs.

○The transfusion of more than 10 units of red blood cells within the initial 24 h period following surgery has been identified as a potential risk factor for death due to hemorrhage.○In cases of hemorrhage or tamponade, reoperation may be required.

NOTE: A hemorrhagic stroke is categorized as a neurological incident, separate from the occurrence of bleeding.

Pericardial fluid trapping.

The term “pericardial fluid accumulation” denotes the accumulation of either fluid or thrombus within the area of the pericardium. In instances where surgery or percutaneous catheter drainage is deemed necessary, this diagnosis must be made. The aforementioned event may be classified further into two categories: firstly, those instances that present with the clinical signs of tamponade, such as an increased central venous pressure and a decreased cardiac output, and secondly, those that do not present with these signs of tamponade.

Arterial non-CNS thromboembolism.

A definitive assessment of an acute systemic arterial perfusion deficit in any non-cerebrovascular organ system resulting from thromboembolism can be achieved through the confirmation of one or more of the evidence-based criteria outlined below:○The patient was subjected to standard clinical and laboratory examinations, as well as an operative evaluation of the relevant findings.○Findings from the postmortem.

The provided delineation does not include occurrences pertaining to the neurological domain.

Wound dehiscence.

The surgical incision has been compromised as a result of an event that did not involve infection. This necessitates surgical repair.

Venous thromboembolic event.

The presence of a venous thromboembolic event, such as deep vein thrombosis or pulmonary embolism, can be identified through the utilization of established diagnostic techniques.

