**Inclusion Criteria**
Age 18 years or older. The patient presented with symptomatic secondary mitral regurgitation (3+ or 4+ by echocardiographic laboratory assessment), which was attributed to cardiomyopathy of either ischemic or non-ischemic etiology. The patient’s condition has been managed in accordance with the relevant clinical guidelines, including those pertaining to coronary artery disease, left ventricular dysfunction and disease, mitral regurgitation, and heart failure. Subjects with at least one hospitalization for heart failure. BNP ≥ 300 pg/mL or a corrected NT-proBNP ≥ 1500 pg/mL. NYHA functional class II or III or ambulatory class IV. Each center’s heart team will decide whether to offer MV surgery or TEER. Left ventricular end-systolic dimension ≤ 70 mm. Left ventricular ejection fraction ≥ 20% and ≤50%. The nature of the primary regurgitant jet is commissural or non-commissural. For the MitraClip group, the implanting investigator’s opinion is that the MitraClip can successfully treat the jet (if a secondary jet is present, it must be considered clinically insignificant). Trans-septal catheterization and femoral vein access is possible with the MitraClip implanting investigator. The subject gave written informed consent and agreed to all the terms of this study and the follow-up visits after the procedure.

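### The definition of reoperation for bleeding is restricted to patients whose sternum was left open, which contradicts its own paragraph and the separate bleeding adverse event

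*Protocol article*

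**What the plan says.** All of this is in the protocol article, mostly in Section 2.3.

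- **Reoperation for bleeding** (perioperative items under the secondary endpoints). The paragraph opens with "A reoperation to reopen the chest for the management of excessive bleeding is indicated in cases where bleeding persists". The defining sentence then limits the event to a procedure needed to "address excessive bleeding in a patient in whom the sternum was left open during the initial operation". The next sentence excludes some procedures, among them "reopening the chest for hemodynamic instability without severe bleeding", as well as pericardial or pleural puncture and chest-tube insertion for retained blood. Supplementary Table S1 is cited for this item and is not shown.
- **Bleeding** (Specific Adverse Event Definitions). A bleeding incident requires one of two items. The first begins "The transfusion of more than 10 units of red blood cells within the initial 24 h period following surgery has been identified" and goes on to call this a possible risk factor for hemorrhagic death. The second reads "In cases of hemorrhage or tamponade, reoperation may be required". Neither mentions the sternum.
- **Pericardial fluid** (same list). This is a category of its own: "In instances where surgery or percutaneous catheter drainage is deemed necessary, this diagnosis must be made". It is split by whether signs of tamponade are present.
- **TEER access** (Table 4, inclusion criteria): "Trans-septal catheterization and femoral vein access is possible with the MitraClip implanting investigator".
- **Group sizes** (Section 3): 384 surgical and 246 transcatheter patients.

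**The concern.** The sentence that defines the event does not fit the text around it. A chest can be reopened only if it was closed, yet the definition admits only patients in whom it was not. A center applying the definition as written would leave out a patient who was closed and then re-explored for bleeding. A center applying the surrounding sentences would count the same patient.

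The bleeding adverse event adds a second rule with a different scope, and its items do not state what has to have happened. The protocol has adverse events adjudicated locally at each center and reports each event type with a 95% confidence interval. Contradictory wording can therefore produce different counts for identical events across five centers. The comparison of this item between groups would also be one-sided, because the definition presupposes a sternotomy.

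**Working it through.** The documents give no bleeding or re-exploration rate, so there is no figure of the plan to reproduce. The check is a comparison of the rules, followed by a simple capture calculation.

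**Step 1. Apply each rule to the same patient.**

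| Patient | Reoperation for bleeding, literal definition | Bleeding adverse event, reoperation item read as a criterion |
|---|---|---|
| Surgery, sternum closed, re-explored for hemorrhage | Not counted | Counted |
| Surgery, sternum left open, further procedure for excessive bleeding | Counted | Counted |
| Surgery, re-explored for tamponade without severe bleeding | Not counted, if taken as instability without severe bleeding | Counted |
| TEER, operated on for hemorrhage | Cannot be counted | Counted |

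The first and fourth rows follow directly from the wording. The third needs an inference, because the reoperation paragraph does not use the word tamponade.

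**Step 2. Check whether the adverse-event items are criteria.** The introductory sentence asks whether one of the listed things has occurred. The transfusion item reports an association with death. The reoperation item says what might become necessary. Death due to hemorrhage appears only as the outcome of the risk factor and not as a criterion of its own. An adjudicator has to guess that the intended events are the transfusion, the death and the reoperation.

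**Step 3. Size of the surgical miscount.** Let r be the true re-exploration rate for bleeding in the 384 surgical patients, and s the share of re-explored patients whose sternum had been left open.

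- True events = 384 × r
- Events captured by the literal definition = 384 × r × s
- Share missed = 1 − s, whatever r is

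Both r and s are assumptions; the documents give neither.

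| r (assumed) | True events | Captured, s = 1% | s = 5% | s = 20% | s = 50% |
|---|---|---|---|---|---|
| 2% | 7.7 | 0.1 | 0.4 | 1.5 | 3.8 |
| 5% | 19.2 | 0.2 | 1.0 | 3.8 | 9.6 |
| 8% | 30.7 | 0.3 | 1.5 | 6.1 | 15.4 |
| Share missed | | 99% | 95% | 80% | 50% |

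**Step 4. TEER.** Access is femoral and trans-septal, so there is no sternum to leave open. The count for this item is 0 of 246 whatever happens to the patients.

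**The case against.** The strongest reply is that this is a local drafting slip in a minor item. Reoperation for bleeding is not in the Section 2.2.2 list of secondary endpoints. All later surgical procedures and all reoperations are to be recorded anyway, and Supplementary Table S1 may hold the working definition. The perioperative item and the adverse event may also be meant to differ in scope. Most of this is fair and limits the weight of the point. It does not remove the contradiction inside the defining paragraph: even if the supplement is sound, the main text disagrees with itself.

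Three stronger readings are tempting, and the documents do not support them.

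- **That nearly all TEER bleeding goes uncounted.** The open-sternum clause governs reoperation for bleeding only. TEER bleeding can still enter through blood loss and transfusion, the bleeding adverse event, drained pericardial fluid (percutaneous drainage is named there) or the serious adverse event rules. The transfusion item is timed from surgery, but Table 5 uses surgical procedure for both S-MVi and TMVi, so that wording does not shut TEER patients out. What can be said is that the Bleeding definition in the main text lists no access-site category; whether Table S1 does is unknown.
- **That most surgical re-explorations are missed.** This holds only if s is below 50%. That may be plausible, but the documents give no basis for it.
- **That fatal bleeding is lost.** Any death counts in all-cause mortality, in MACE and as a serious adverse event. What is missing is a bleeding criterion for it.

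On tamponade, the objection is right that the conflict is inferred. Reopening for tamponade with severe bleeding falls outside the exclusion. The case without severe bleeding is left unsettled between the two rules.

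**Conclusion.** The point holds as a contradiction in a stated outcome definition. Taken literally, the open-sternum clause omits every re-exploration for bleeding after a closed sternum and makes the item impossible to meet in TEER. It also disagrees with the sentences around it and with the bleeding adverse event. In surgery the loss is 1 − s of the true events, with s unknown. In TEER the count is zero by construction for this item alone. The two bleeding adverse-event items need rewording before they can be adjudicated.

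The consequence is confined to a perioperative secondary measure and a safety category. The primary endpoint, all-cause mortality, MACE and the sample size are not touched. The conclusion rests on the main text as printed; Supplementary Table S1 could not be checked.

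**What to change.** 1. In the reoperation-for-bleeding definition, remove the open-sternum restriction. A reoperation for excessive bleeding should count whether or not the sternum had been closed, in either group, timed from the index procedure.
2. Reconcile that definition with the bleeding adverse event, and with Supplementary Table S1 if it differs. State whether re-exploration for tamponade without severe bleeding counts as bleeding or only as the pericardial-fluid event. A blanket rule counting every return for tamponade is not proposed, since it could override the existing exclusions and double-count the pericardial-fluid category.
3. Reword the bleeding adverse event as separate criteria: red-cell transfusion above the stated 10 units in 24 h, death due to hemorrhage, and reoperation for hemorrhage.

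The cost is the wording of two definitions and the recoding of reoperations and transfusions that the registry already records. No extra patients or procedures are needed. Reported surgical rates may look less favourable.

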#### 2.2.2. Secondary

A number of secondary endpoints will be subjected to evaluation in the context of the forthcoming trial. The trial will evaluate the primary secondary endpoint, which is all-cause mortality. This endpoint offers supplementary clinical data to the primary physiological endpoint, enabling an evaluation of the overall efficacy of the treatment. Moreover, the subsequent secondary endpoints have been delineated for the trial.

▪Functional Status, Hospitalizations, and Neurocognition.NYHA classification.MACE (death, stroke, worsening heart failure (+1 NYHA Class), CHF hospitalization, mitral valve re-intervention).Angina class.Neurocognitive results.Peak VO2 (assessed by a cardiopulmonary stress test).The rates of patients readmitted within 30 days and the long-term readmission rates for all patients, as well as for those with cardiovascular issues and heart failure, are to be determined. Furthermore, the proportion of days spent outside of the hospital setting during the follow-up period following survival will be determined.LOS for the hospital stay and discharge destination.
▪Physiologic Measures.Echocardiography assessment.Quantification of MR, specifically the effective regurgitant orifice area (ERO).Quantifying mitral valve area.LV size, function, and geometry (including LVEF, LVEDD, LVESD, LVEDVI, LVESVI, and LV sphericity).Assessment of mitral valve and subvalvular structures.LA dimension.RV size and function.MV tethering.Assessing regional wall motion for left ventricular function and viability.Appropriate revascularization.▪Safety.
Incidence of serious adverse events.Reoperation for MR and freedom from reoperation in general.▪Perioperative Measures.Operative time for each procedure. For the standard surgical mitral valve operation, cardiopulmonary bypass (CPB) and cross-clamp time are required.Blood loss and transfusion.▪Quality of Life and Economic Measures.
Change in quality of life (QOL).Minnesota Living with Heart Failure (MLHF) score.SF-12.EuroQoL.Dasi.

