### 2.3. Therapeutic Interventions

In order to provide the most accurate and comprehensive assessment of primary and secondary endpoints, two distinct patient subgroups will be examined. The initial cohort will consist of patients who underwent TEE) or S-SMVp in conjunction with coronary revascularization, specifically PCI or CABG. The subsequent cohort will comprise patients who did not receive revascularization [14,15,16,17].

▪Standard Mitral Valve Intervention (S-MVi) (S1 Supplementary Material).•Mitral valve replacement (MVrpl).

MVrpl entails the preservation of the subvalvular apparatus with the objective of preventing LV diameter enlargement over time. The decision as to whether to utilize a preservation technique, prosthetic valve type, and suture positioning is at the discretion of the surgeon. In cases of ischemic cardiomyopathy, CABG is a requisite procedure for revascularization.

Restrictive mitral annuloplasty.

An RMA can be carried out with the use of a complete rigid or semi-rigid annuloplasty ring that has been reduced in size to align with the annulus diameter. Given that patients who receive RMA frequently present with CAD, a CABG procedure may be required to facilitate optimal LV remodeling.

Restrictive mitral annuloplasty plus subvalvular repair.

RMA may be in conjunction with the use of SV-r. Subvalvular Repair allows for the approximation or relocation of papillary muscles that are displaced by post-infarction scar formation. In individuals who have undergone SV-r due to ischemic cardiomyopathy, CABG is a necessary subsequent procedure.

▪Transcatheter Mitral Valve Intervention (TMVi) (S2 Supplementary Material) [21,22,23,24,25,26,27,28,29,30,31,32,33,34].•Transcatheter edge-to-edge repair (TEER).

The TEER intervention entails the convergence of the margins of the anterior and posterior leaflets of the mitral valve, a process known as edge-to-edge repair. In the event that a single MitraClip device is insufficient to achieve the desired reduction in MR, a subsequent implant may be employed to optimize the intervention.

▪Endpoint Definitions and Measurement.•Primary endpoint.

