The objective of this study is to evaluate improvements in quality of life (QOL) from baseline utilizing a comprehensive array of disease-specific instruments. These include the Minnesota Living with Heart Failure (MLHF) score, the disease-specific Duke Activity Status Index (DASI), the Short Form-12 general health status index, and the EuroQol 5-D measures of health state preference, with an emphasis on both individual and societal perspectives.

The Minnesota Living with Heart Failure Questionnaire is a quantitative assessment tool designed to evaluate the impact of heart failure and its management on patients across a range of domains, including physical, psychological, and social functioning. The DASI is a multidimensional questionnaire that assesses the cardiovascular impact of four domains of adult activity, each associated with distinct levels of oxygen uptake: ambulation, personal care, domestic tasks, sexual function, and the pursuit of leisure activities. The SF-12 represents a comprehensive quality-of-life assessment tool encompassing eight distinct dimensions: physical activity, social activity, role/physical, body pain, general mental health, role/emotional, vitality, and general health perception. The SF-12 and the EuroQoL 5-D are both instruments designed to assess health-related quality of life. The EuroQol 5-D is a psychometric instrument that yields a succinct descriptive profile comprising five distinct dimensions. The instrument evaluates five domains: (i) anxiety/depression, (ii) pain/discomfort, (iii) usual activities, (iv) self-care, and (v) mobility. Furthermore, it incorporates an evaluation of the individual’s perception of their own health status.

▪Safety.
•Reoperation.•All reoperations, particularly those for mitral regurgitation, will be recorded. Freedom from reoperation will be evaluated.•Adverse events.

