A total sample population of 630 patients was calculated as sufficient to detect a significant difference in the rate of reverse left ventricular remodeling, with 384 patients undergoing surgical mitral valve repair and 246 patients undergoing transcatheter mitral valve repair. This study was powered at 80% with a two-tailed alpha level of 0.05. In order for a *p*-value to be deemed statistically significant, it must be less than 0.05. All statistical analyses were performed with the aid of the R software package developed by the R Foundation for Statistical Computing in Vienna, Austria.

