**Probable**
The following attributes will be applicable to the adverse events in question that are deemed, following a meticulous medical assessment, to be linked to the surgical procedure (S-MVi or TMVi) with a high degree of reliability. There is a clear temporal relationship between the event and the surgical procedure. The event is a representative example of the typical postoperative course, which can be ascribed to a commonly observed underlying condition among the general population or individual. The incident in question is not a documented outcome of the surgical intervention in question, and there is no reasonable basis for attributing it to an alternative cause

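### The reoperation endpoint is worded in surgical terms and does not match the MACE re-intervention term; on its natural reading, a later repeat clip would not count while a repeat operation would.

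*Protocol article*

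**What the plan says.** The protocol article describes repeat procedures in four places and does not use one term.

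- **Section 2.2.2, Safety** lists "Reoperation for MR and freedom from reoperation in general", without a definition.
- **Section 2.3, Functional Status, Reoperation** has the only operative wording: "All subsequent surgical procedures, including reoperations for MR, will be meticulously documented, and the incidence of reoperation will be evaluated". A time-to-event analysis is specified.
- **Section 2.3, Safety, Reoperation** says "All reoperations, particularly those for mitral regurgitation, will be recorded. Freedom from reoperation will be evaluated". It neither limits this to surgery nor extends it to transcatheter procedures.
- **Section 2.2.2, MACE** (repeated in section 2.3) uses a different, wider term: "MACE (death, stroke, worsening heart failure (+1 NYHA Class), CHF hospitalization, mitral valve re-intervention". The component is not defined further.

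None of these states whether a repeat TEER, or any other later transcatheter mitral procedure, is a reoperation event.

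**The concern.** The study compares a transcatheter treatment with surgery, and how long the correction lasts is one of the things a reader will look for. The second treatment after a failure can differ by arm: a failed TEER may be given another clip, a failed surgical repair another operation. If the endpoint is restricted to surgery, it partly measures the route of re-treatment and not whether the first treatment failed.

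This would be an error in what counts as an event. Propensity weighting does not remove it, and neither does a larger sample. The reoperation result and the MACE re-intervention component could also disagree for reasons of definition alone, and centers could code the same repeat clip differently.

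**Working it through.** **1. Which reading does the text favour?**

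*For surgery-only:*
- The operative sentence speaks of surgical procedures.
- The definition of reoperation for bleeding in section 2.3 uses nearly the same phrase for reopening the chest, which is open surgery.
- The inclusion criteria (section 2.1.2) set a surgical approach against a transcatheter technique, and the sample-size paragraph (section 3) does the same: "with 384 patients undergoing surgical mitral valve repair and 246 patients undergoing transcatheter mitral valve repair".
- MACE, in the same endpoint section, uses re-intervention where a wider count is meant.

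*Against it:*
- The operative sentence does not say that only surgery counts.
- The Safety paragraph refers to all reoperations.
- Table 5 describes probable adverse events as those judged "to be linked to the surgical procedure (S-MVi or TMVi) with a high degree of reliability", so there the term covers both arms.

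Surgery-only is the more natural reading of the endpoint sentence, because Table 5 is a causality scale and not an endpoint definition. It is still a reading and not an express rule.

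**2. What would the surgery-only reading do?**

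The document gives no re-treatment rate, so there is no stated figure to reproduce. What follows is an illustration.

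Inputs from the document: 384 surgical and 246 transcatheter patients, two-sided alpha 0.05 (section 3).

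Assumptions not in the document:
- the true re-treatment risk r is the same in both arms;
- a share s of TEER re-treatments is by repeat clip and is not counted;
- all surgical re-treatments are operations and are counted.

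Apparent TEER risk = r × (1 − s). Apparent hazard ratio (TEER versus surgery, proportional hazards) = ln(1 − r(1 − s)) / ln(1 − r).

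For r = 10%:
- s = 25%: apparent TEER risk 7.5%; ln(0.925)/ln(0.90) = 0.0780/0.1054 = 0.74.
- s = 50%: apparent TEER risk 5.0%; ln(0.95)/ln(0.90) = 0.0513/0.1054 = 0.49.

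The true hazard ratio is 1.0 in both cases.

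The chance of a falsely significant result favouring TEER, from a simple unweighted two-proportion test with 384 versus 246 patients, is about:

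| True risk r | s = 25% | s = 50% | s = 75% |
|---|---|---|---|
| 5% | 10% | 33% | 73% |
| 10% | 18% | 62% | 97% |
| 20% | 35% | 93% | over 99% |

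This test is not the planned weighted analysis, and it ignores censoring and death as a competing event. It shows the order of magnitude only.

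**3. Can the direction change?**

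Yes. If a share t of surgical re-treatments is done by catheter and also goes uncounted, the apparent risk ratio becomes (1 − s)/(1 − t). At s = t = 50% it is 0.5/0.5 = 1, with no distortion. At s = 50% and t = 25% it is 0.5/0.75 = 0.67. The tilt is towards TEER only while s exceeds t.

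**The case against.** **A repeat clip is not expressly excluded.** A reader might infer that the endpoint counts only surgery and that a repeat clip is definitely not an event. The document does not go that far, for the reasons set out in the working. Section 2.2.2 also lists operative time for each procedure before adding bypass and cross-clamp times for surgery, so operative language reaches TEER there too. This stands: the defect is an ambiguity whose natural reading is unequal, and not a demonstrated exclusion.

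**Repeat clips are captured elsewhere.** On its plain meaning the MACE component includes a repeat clip in either arm, and MR is measured by echocardiography. This stands as far as data collection goes. It does not repair the separately reported reoperation endpoint.

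**A later clip might be booked as index treatment.** A reader might infer this from the TEER description, which says that "a subsequent implant may be employed to optimize the intervention". The sentence opens with the case of a single device giving too little MR reduction and describes how TEER is performed. Nothing links it to event counting, so it does not support the claim that later clips escape MACE.

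**General freedom from reoperation burdens surgery.** Re-exploration for bleeding and repair of wound dehiscence do arise mainly from open surgery. Counting them in a general safety measure is nevertheless legitimate; reoperation for MR is listed separately, and bleeding and dehiscence have their own definitions. What remains is a reason to report them apart from mitral failure.

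**An article may leave event rules to a fuller document.** That is fair for fine detail, and the cited supplementary material is not at hand. The mismatch between the two terms, however, is in the text that the article does state.

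**Conclusion.** The concern holds as an ambiguity with an unequal natural reading. Followed that way, the reoperation endpoint would count a repeat operation for recurrent MR but not a later repeat clip for the same failure, and the comparison would tilt towards TEER. The size is unknown. The illustrated hazard ratios of 0.74 and 0.49 rest on assumed rates and on all surgical re-treatments being operations; transcatheter re-treatment of surgical patients would reduce or reverse the effect.

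The endpoint affected is a further secondary/safety item. The primary endpoint (LVEDVI at 10 years), the main secondary endpoint (all-cause mortality) and the sample size are untouched. The wording should be settled before analysis, so that results cannot influence the choice of definition, but it does not threaten the study's main conclusion.

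**What to change.** 1. For the durability comparison, replace reoperation for MR in sections 2.2.2 and 2.3 with: *any mitral valve re-intervention, surgical or transcatheter, after completion of the index procedure*.
2. Use the same definition, in both arms, for the MACE component.
3. State that a clip placed in a later, separate procedure is a re-intervention.
4. Report surgical re-intervention, transcatheter re-intervention and non-mitral re-exploration (bleeding, wound) as separate descriptive components.

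The cost is protocol wording, since mitral re-interventions already have to be collected for MACE. The small downside is that the TEER event rate may look less favourable than under a surgery-only count.
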